### Outcomes and measures

The primary and secondary outcomes are described in more detail below. Table 2 shows an overview of all measures and their survey times (which, when and how).

#### Primary outcomes

Data on asthma self-management at work as well as behavioural intention regarding asthma self-management at work (and workplace-related self-efficacy, see below) are collected in the same questionnaire.

##### Asthma self-management at work

Self-management is measured by a questionnaire devised [4] and previously used by our group [6]. It consists of ten items on trigger avoidance (1 item), acute symptom management (7 items, e.g., reliever medication use, breathing techniques, or taking breaks), and communication (2 items, referred to self-disclosure). For example, the following item relates to acute symptom management: “When my asthma at work is triggered by a certain situation, I leave that situation.” (for the full questionnaire, see Heinrichs et al., 2019 [6]). The response categories include the following: “Yes, I do this”, “No, but I would like to”, and “No, I do not need this”.

##### Behavioural intention

Behavioural intention is intended to measure the willingness to implement (for the first time or continued) self-management strategies in the workplace. For each self-management item, we ask the following in this context: “I plan to do this in the future (for the first time or continue).” Response categories include a 5-point Likert scale ranging from − 2 (“does not apply at all”) to + 2 (“fully applies”).

#### Secondary outcomes

##### Self-efficacy

Job-related self-efficacy is conceptualized in this study as referring to the belief that one feels capable of implementing self-management strategies at work as desired by oneself. For each item of the three subscales (trigger avoidance, acute symptom management, communication), we developed an associated item on self-efficacy: “I trust myself to do this in the future (for the first time or further).” The response categories correspond to those for behavioural intention (see above).

##### Self-management-related knowledge

Newly acquired knowledge of asthma self-management at work will be assessed by 20 items (potential score: 0–20). The items relate to the content of the intervention module and can be divided into four subscales: (1) asthma self-management at work in general, (2) rights as an employee, (3) job crafting, and (4) successful communication (with supervisors and colleagues). Each item is to be answered with “true” or “false”.

##### Number of asthma-related sick days

To examine the number of days of incapacity, we will ask the following question: “How many working days within the last three months (T3: since the end of rehabilitation) were you not able to work due to your asthma and… a)…called in sick (without a sick note)? b)…got a sick note from your physician?”

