We hypothesise that the behavioural intention related to the implementation of appropriate asthma self-management will improve at the end of the rehabilitation program (T2). As mentioned above, the behavioural intention is considered a key determinant of successful asthma self-management at work [15, 20]. Then, after 3 months and the possible return to work (T3), actual asthma self-management at work should have improved due to prior proactive initiation of changes of relevant individual working conditions. Thus, behavioural intention will be used as primary outcome at T2 while asthma self-management will serve as primary outcome at T3. Self-management-related knowledge and self-efficacy along with other factors (see below) will represent the secondary outcomes. The potential improvement in asthma self-management at work and related improvement in asthma control, asthma-related quality of life, and the subjective employment prognosis (see above) [6, 7] could then reduce the number of exacerbations and sick days (and also related costs). Therefore, we will also examine asthma control, asthma-related quality of life, the subjective employment prognosis, and the number of exacerbations and sick days as secondary outcomes.

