## Methods/design

### Study design and data collection

A randomized-controlled intervention study will be carried out comparing the intervention group (patient education “Asthma and Work”) with a control group (patient education “Eating behaviour”, parallel group). We estimate that in total about 180 individuals with asthma will participate in two rehabilitation clinics in Germany (Hufeland-Clinic Bad Ems: *n* ≥ 60, Clinic Bad Reichenhall: *n* ≥ 120) over a period of 15 months (recruitment, implementation, 3-month follow-up). Initially, screening for eligibility for participation takes place approximately four weeks before the start of inpatient pulmonary rehabilitation (T0). Furthermore, measurements at the beginning (T1) and at the end of rehabilitation (T2, about three weeks after T1) as well as a follow-up survey (T3, about three months after T2) are planned (see also Table 1). The data are collected primarily by using a patient questionnaire (self-reports). In addition, medical data are collected at T1 and T2 by the rehabilitation staff (physician questionnaire). The study is coordinated at the University of Duesseldorf, Germany, by the study coordinator (JS) and the study director (AL) (e.g., development of the intervention and control module, study materials, data management and statistical analysis, access to the final dataset). On-site study procedures are carried out by study assistants (e.g., recruitment, management of assignment lists of ID and contact data, documentation of drop-outs or deviations from intervention protocol, a reminder to participate at T3 by phone), and patient education is facilitated by (pre-trained) psychologists. To ensure that our study protocol reports all relevant content, we applied the SPIRITreporting guidelines [21]. The study was registered in the German Clinical Trials Registry (ID: DRKS00031843) on 17.10.2023.

**Table 1 Tab1:** Time schedule

2023					2024												2025			
Aug	Spt	Oct	Nov	Dec	Jan	Feb	Mar	Apr	May	Jun	Jul	Aug	Spt	Oct	Nov	Dec	Jan	Feb	Mar	Apr
1	2	3	4	5	6	7	8	9	10	11	12	13	14	15	16	17	18	19	20	21
Preparation intervention and control module, development of education materials																				
					Screening (T0) + recruitment															
						Pre-test^1^														
						Implementation phase (T1 + T2)														
							3-month follow-up (T3)													
							Data management and analyses													
													Paper							

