### Patient selection

Four weeks before rehabilitation, all patients with the primary diagnosis of asthma will be contacted by mail and asked to complete the screening questionnaire. Patients will be included in the study if they meet the following criteria (see also Table 2), which are assessed using the screening questionnaire (and partially verified by a physician questionnaire at the start of rehabilitation). All patients receive the usual rehabilitation programme, regardless of whether they take part in the study or not.

Referral diagnosis “bronchial asthma”: diagnosis before the start of the pandemic (before March 2020)^1^ + confirmation of the diagnosis (ICD-10 code J45) in the rehabilitation clinic by a pulmonologist based on clinical and lung function diagnostics with spirometry/body plethysmography at T1 (forced expiratory volume in 1 s [FEV1], FEV1/vital capacity [VC], total specific airway resistance [sR_tot_], VC, residual volume [RV]), supplemented by allergy screening (total immunoglobulin E [Ig E], specific Ig E-screening), assessment of exercise capacity (6-minute walk test) and asthmatic inflammation (fractional exhaled nitric oxide [FeNO], eosinophils/µl)Employment in an employee or civil servant relationship subject to social insurance with at least 15 h of work per week.Worked with the asthma diagnosis for at least six months.

Individuals with referral diagnosis of Chronic Obstructive Pulmonary Disease (COPD) or long/post COVID (longer-term, adverse health effects following SARS-CoV-2 infection) are excluded. Mixed leading asthma and COPD cases are accepted as long as asthma is the referral diagnosis. Similarly, individuals with additional self-reported persistent long/post COVID symptoms (e.g., fatigue) remain in the study, but– like individuals with mixed asthma-COPD– are excluded in a sensitivity analysis (see below). If all inclusion criteria are met, study participation is usually only discontinued at the participant’s request.

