## Discussion

Observational data suggested that psychosocial working conditions are associated with asthma self-management at work among employed individuals who are undergoing inpatient rehabilitation for asthma [4, 5]. Key working conditions included social support and job decision latitude, i.e., the extent to which work tasks and times can be determined at one’s own discretion [4, 5]. To our knowledge, experimental data from pulmonary rehabilitation on this issue are lacking. The aim of this study is therefore to develop and implement a novel patient education module that seeks to empower individuals with asthma to modify their working conditions in order to maximize their opportunities for appropriate asthma self-management at work.

Based on the assumption that the expected effects are observed, the patient education module could increase, amongst others, work ability, and social participation, improve return to work or staying at work, and reduce the number of sick days by improving asthma self-management as well as asthma control and asthma-related quality of life. Improving asthma self-management at work, but also asthma control and asthma-related quality of life [6, 7], could reduce costs associated with, e.g., asthma-related disability and early retirement. Ultimately, a patient education module should be available that is not only applicable to rehabilitation patients with asthma, but could also be evaluated in outpatient settings (e.g., disease management programs) or adapted to other chronic conditions.

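### Sick days cover a fixed three months at T1 but an open window at T3, and the analysis ignores elapsed time

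*Protocol article*

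**What the plan says.** The section on the number of asthma-related sick days gives the item: "How many working days within the last three months (T3: since the end of rehabilitation) were you not able to work" because of asthma. Two sub-questions separate days with and without a physician's note. The bracket replaces the three-month recall period at T3 with one that begins at the end of rehabilitation. It has no stated end other than the moment of answering.

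The section on study design and data collection sets the timing: a "follow-up survey (T3, about three months after T2) are planned". The study assistants' duties there include "a reminder to participate at T3 by phone".

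The data analysis plan lists the number of sick days among the secondary outcomes. Changes from T1 to T3 are tested within each arm by paired t-tests. Arms are compared by ANCOVA on the follow-up value, adjusted first for the baseline value and then also for clinic, gender, age and education. Change scores come in where baseline and follow-up correlate above 0.5. Time between the end of rehabilitation and the T3 response appears in none of these models. Table 2 collects information on occupation at T3, but the described sick-day analysis does not use it.

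**The concern.** A count of days missed grows with the length of the period over which it is taken. The T1 count comes from the same length of time for everyone, while the T3 count comes from whatever time each participant let pass before answering. The paired comparison therefore sets two different quantities against each other. A participant whose sick-leave rate has not changed shows a worsening if late and an improvement if early. A real fall in the rate can be hidden in the same way.

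Between arms the issue is milder. Unequal windows add variation unrelated to treatment, and they would bias the comparison if one arm tended to answer later than the other.

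At stake is how the sick-leave result is read. The abstract gives asthma-related sick leave as its example of a possible cost reduction, and the Discussion hopes that the module might "improve return to work or staying at work, and reduce the number of sick days".

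**Working it through.** **The plan's own figures.** The article gives no expected number of sick days, no T3 window width and no sample-size figure for this outcome. Its only sample-size calculation reproduces (300 × (1 − 0.40) = 180) and does not concern sick days.

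**Inputs.** From the article: a T1 window of 3 months (13 weeks), a T3 window from the end of rehabilitation to the response, and 90 per arm at T3. Assumed, because the article gives none: a constant rate of 5 days per 3 months, and the response times below.

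**Step 1: one participant, unchanged rate.** Expected T3 count = rate × window, so the ratio to the T1 count is window / 3 months.

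| T3 answered at | Ratio to T1 | Expected days (T1 = 5.00) |
|---|---|---|
| 2.5 months | 2.5/3 = 0.83 | 4.17 |
| 3 months | 1.00 | 5.00 |
| 3.5 months | 3.5/3 = 1.17 | 5.83 |
| 4 months | 4/3 = 1.33 | 6.67 |
| 5 months | 5/3 = 1.67 | 8.33 |

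In weeks, 17/13 = 1.31, a 31% higher expected count. The ratios do not depend on the assumed 5 days.

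**Step 2: the paired test.** At an unchanged rate, the mean change within an arm is rate × (mean T3 window − 3 months). With a mean window of 3.5 months, each arm shows an apparent rise of 5.83 − 5.00 = 0.83 days. Equivalently, a true fall in the rate of 1 − 3/3.5 = 14% would show as no change. If early and late answers average out at three months, the mean change is right and only noisier.

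**Step 3: between arms.** At equal rates, the spurious difference is rate × (mean window in one arm − mean window in the other). If both arms average 3.5 months it is 5.83 − 5.83 = 0. A simulation checked this with 90 per arm, negative binomial counts with mean 5 and dispersion k = 0.4 (both assumed), 20,000 runs and a two-sample t-test. There was no true rate difference, and one common window applied within each arm.

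| Windows | Rejection rate |
|---|---|
| Three months in both arms | 0.048 |
| 33% longer in both arms | 0.051 |
| 17% longer in one arm | 0.09 |
| 33% longer in one arm | 0.20 |

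**Step 4: the noise.** With the same assumed distribution, the variance at a three-month window is 5 + 5²/0.4 = 67.5. Suppose half of each arm answers at 2.5 and half at 3.5 months. The relative variance of the window is (0.5/3)² = 0.028, and the variance of the count becomes 5 + 62.5 × 1.028 + 25 × 0.028 = 69.9. That is about 4% more, so the loss of precision is small at that spread.

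**The case against.** **Level of detail.** Offsets and exposure time are often left to an analysis plan, which is not shown here. That would excuse silence. But the article fixes both recall windows in the item wording and names the tests applied to the count. The listed fallbacks (a robust regression or a log transform) are only examples, but they are triggered by violated model assumptions and do not address elapsed time.

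**The T3 anchor has a reason.** Starting at the end of rehabilitation keeps the inpatient stay and earlier time out of the follow-up count. This stands. The anchor can stay; what is missing is an allowance for where the window ends.

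**Randomised arms share the item and the reminder.** This also stands. Nothing in the article suggests that response timing differs by arm, and a telephone reminder does not establish month-long delays. The 31% describes one late participant and is not an effect on the trial's comparison.

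**A stronger reading.** A reader might infer that participants who have left work score zero, the best value, so that the arm with better job retention looks worse. With an assumed 5 days per worker and leavers coded zero, 5% leavers in the intervention arm against 15% in control gives 5 × 0.95 = 4.75 against 5 × 0.85 = 4.25, a ratio of 1.12. The documents do not support this as a finding:

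- The article does not say how someone without a job answers the item or how the answer is coded. A blank would drop out of the complete-case analysis.
- The phrase "after 3 months and the possible return to work (T3" follows an inpatient stay and does not mean loss of employment. Someone still employed but off work with asthma would report many days.
- Entry requires current employment, and the article gives no rate of leaving it. Equal shares give a ratio of 1.00, and 20% in the intervention arm against 10% in control gives 0.80/0.90 = 0.89, the opposite direction.

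**Restricting the analysis to time in employment.** Employment at T3 is measured after randomisation and could itself be affected by the module. Making it the denominator of the main sick-day analysis would select on it and depart from the all-as-randomised principle of the data analysis plan. This objection holds and shapes the fix.

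**Conclusion.** The concern holds in a limited form. The T1 and T3 counts cover different lengths of time, and no stated analysis corrects for it, so the T1 to T3 change is not like for like even when both arms respond equally late. At a constant rate the distortion is proportional to the delay. How far it moves the arm means depends on the mean response time, which the article does not give.

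The comparison between arms, which is the test of effectiveness, loses some precision. Bias there would require response timing to differ by arm, which is possible but not shown. Claims that leavers score zero or that the result points the wrong way remain conditional on assumed coding and leaver shares. The matter affects one secondary outcome, and no conclusion on behavioural intention or asthma self-management at work depends on it.

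**What to change.** Analyse T3 sick days per unit of elapsed time for all randomised participants with data, where elapsed time is the T3 completion date minus the date rehabilitation ended. Either of two forms serves:

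- Scale the count to three months (count × 13 / weeks elapsed), which matches the T1 window and leaves the planned paired t-test and ANCOVA in place.
- Fit a count model with the logarithm of elapsed time as offset.

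At a constant rate the ratio of T3 to T1 then becomes 1.00 at every response time, in place of 0.83 to 1.67 for answers between 2.5 and 5 months.

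Record the T3 completion date if this is not already done; Table 2 does not list it. Report by arm the number no longer employed at T3, and state how their answers to the item are handled. A rate restricted to time in employment may be added as a supportive analysis only.

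The cost is one date field and slightly more analysis work. The questionnaire wording, sample size and primary analyses do not change.

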##### Number of asthma exacerbations

To examine the number of exacerbations, we will ask the following questions: “In the last three months (T3: since the end of rehabilitation), have you had at least one asthma attack (significant shortness of breath and use of reliever medication)?” and “In the last three months (T3: since the end of rehabilitation), have you experienced at least one significant worsening of your asthma over at least a few days (‘acute worsening’, ‘exacerbation’)?”

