The following describes the analyses in detail: Descriptive statistics, including means for continuous variables and proportions for categorical variables, will be used to summarize participant characteristics. We will determine the potential changes in primary and secondary outcomes (T1 to T2, T1 to T3) by pre-post comparisons within groups and test them for statistical significance using paired t-tests. Differences between groups (at T2 and T3) will be evaluated using univariate analyses of covariance (ANCOVAs). That is, membership in the intervention or control group will be used as the independent variable in each case, and the follow-up score of the primary outcome measures (behavioural intention, asthma self-management at work) and secondary outcome measures (self-efficacy, self-management-related knowledge, number of sick days, number of exacerbations, asthma control, asthma-related quality of life, and subjective employment prognosis) will be used as the dependent variable. Initially, only the corresponding baseline value of the primary outcome variable is included as a covariate to remove conditional bias [45, 46]. In a next step, the rehabilitation clinic [47], gender, age [48], and education [48] are additionally included as covariates. If the correlation between baseline and follow-up values is high (> 0.5), change scores are used as independent variables instead of follow-up values, as these then provide a more precise estimate [49]. For all models, the statistical model assumptions (linearity, homoscedasticity, normality of residuals) are tested. If the model assumptions are violated, appropriate analysis methods (e.g., robust regression, log transformation) are applied. In addition, to test whether comorbid COPD or long/post COVID disease affects the outcomes, sensitivity analyses will be performed excluding participants with COPD and/or long/post COVID symptoms. We will also conduct the analyses again without those who participated during the pre-test^2^, as at this point there may not yet be a routine regarding the training procedures and minor adjustments may still be made. Gender-stratified analyses are also conducted. Likewise, those with uncontrolled (ACT < 20 [32]) versus controlled asthma (ACT ≥ 20 [32]) and those with versus without a need for medical-occupational rehabilitation^3^ should additionally be analysed separately. Our primary analysis will be based on complete case analysis. In case the proportion of missing data exceeds 5% on a given variable, we will carry out sensitivity analysis employing multiple imputations.

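### The secondary outcome is called the number of exacerbations, but the patient items at T1 and T3 ask only whether at least one event occurred, so no number can be derived

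*Protocol article*

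**What the plan says.** **Outcome name.** The Abstract, the Background, the section on the number of asthma exacerbations and the Data analysis plan all speak of a number of exacerbations. The Background gives the rationale: better self-management and the improvements that go with it "could then reduce the number of exacerbations and sick days".

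**Items.** The outcome section opens with "To examine the number of exacerbations, we will ask the following questions". The first asks "have you had at least one asthma attack". The second asks "have you experienced at least one significant worsening of your asthma over at least a few days". Both cover the last three months or, at T3, the time since the end of rehabilitation. Neither asks how many.

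**Neighbouring item.** The sick-days item does ask for a count: "How many working days within the last three months".

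**Analysis.** The Data analysis plan states: "Differences between groups (at T2 and T3) will be evaluated using univariate analyses of covariance (ANCOVAs"). The dependent variables include "number of sick days, number of exacerbations, asthma control, asthma-related quality of life, and subjective employment prognosis". Within-group changes in primary and secondary outcomes are tested with paired t-tests. If model assumptions fail, appropriate methods are to be used, with robust regression and log transformation as examples. Half a standard deviation of the change score is adopted as the yardstick of clinical relevance, with no outcome excepted.

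**Timing.** Table 2 lists exacerbations at T1, T2 and T3. The T2 entry is marked as assessed by a physician, and the wording of that item is not shown.

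**The concern.** The outcome name, the item wording and the analysis are all printed, and they do not fit together. An answer to an at-least-one question is 0 or 1. A participant who goes from six attacks to one answers yes both times and is recorded as unchanged. A mean number of exacerbations computed from such answers would be a proportion under the label of a count, and a reader of the results could not tell.

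Three further consequences follow:

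- The group coefficient from the planned ANCOVA is a difference in proportions, which answers a different question from the one announced.
- A half-SD-of-change threshold has no sensible meaning for a variable whose individual change can only be −1, 0 or +1.
- If events are frequent, a real fall in their number may hardly move the share of participants with at least one.

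**Working it through.** **1. Can a count be recovered?** Each item gives 0 (none) or 1 (one or more). Adding the two gives 0 to 2, but the article states no such sum. It would not be a count either: one episode can earn a yes on both items, and six attacks score the same as one. The T2 physician assessment could conceivably record a number, but it supplies neither the T1 baseline nor the T3 follow-up.

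**2. What the ANCOVA estimates.** With a 0/1 dependent variable, the adjusted group difference estimates the difference between arms in the probability of at least one event.

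**3. The half-SD rule, if applied.** For a 0/1 item with prevalence p at both times and T1–T3 correlation r, half the SD of change is 0.5 × √[2p(1−p)(1−r)]. The article gives neither p nor r; assume p from 0.3 to 0.6 and r from 0.2 to 0.6.

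- Smallest: p = 0.3, r = 0.6: 0.5 × √(2 × 0.21 × 0.4) = 0.205
- Largest: p = 0.5, r = 0.2: 0.5 × √(2 × 0.25 × 0.8) = 0.316

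The threshold would be a shift of about 20 to 32 percentage points in the share with any event.

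**4. Information lost.** The Sample size section gives 300 × (1 − 0.40) = 180 completers, 90 per group, which reproduces. It gives no exacerbation rate, so the rates below are assumptions: control mean m events over about three months, 30% lower in the intervention arm, two-sided 0.05, no baseline adjustment, dispersion k (k = 0 is Poisson).

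- Probability of any event: 1 − exp(−m) if k = 0, otherwise 1 − (1 + km)^(−1/k)
- Yes/no power: Φ(|p0 − p1| / √[p0(1−p0)/90 + p1(1−p1)/90] − 1.96)
- Count power: Φ(|ln 0.7| / √[(1/m + k)/90 + (1/(0.7m) + k)/90] − 1.96)

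| m | k | p0 | p1 | Yes/no power | Count power |
|---|---|---|---|---|---|
| 0.5 | 0 | 0.393 | 0.295 | 29% | 34% |
| 1 | 0 | 0.632 | 0.503 | 42% | 58% |
| 2 | 0.5 | 0.750 | 0.654 | 29% | 62% |

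Worked for m = 1: the difference is 0.129 with standard error 0.073, so z = 1.76 and power is Φ(1.76 − 1.96) = 42%. For counts the standard error of the log rate ratio is 0.164, so z = 0.357/0.164 = 2.17 and power is Φ(2.17 − 1.96) = 58%.

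The loss is small when events are rare and large when they are frequent.

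**The case against.** **The planned test is not invalid.** A reader might infer that ANCOVA on a 0/1 outcome gives a misleading comparison of the arms. It does not. In a randomised comparison it is a linear probability model. Simulated with 90 per arm, a binary baseline covariate, an assumed latent T1–T3 correlation of 0.6 and event rates of 20% to 70%, its type I error was 4.6% to 5.1% and its estimate essentially unbiased. This stands: the fault lies in what is estimated and how it is labelled.

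**The fallback is open-ended.** Robust regression and log transformation are only examples, so a binary model is not ruled out, and an analysis plan not shown may name one. This stands for the choice of model. It does not help with the count, which no analysis can restore.

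**The relevance rule does not name exacerbations.** True. It is worded for observed effects in general, so the 20 to 32 points apply only if it is used here.

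**The power figures are hypothetical.** They rest on assumed rates, treat recalled counts as free of error and leave out the planned baseline adjustment. With that adjustment, and the same assumed correlation of 0.6, yes/no power at a mean of 1 is about 47 to 49% rather than 42%. The trial is not powered on this outcome in any case.

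**The trial's claim does not rest on this.** A reader might infer that a stated hypothesis becomes untestable. The Background says only that exacerbations could fall as a later consequence; its hypotheses concern behavioural intention at T2 and self-management at T3.

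**The T2 physician assessment.** It means the patient items are not the sole source on exacerbations, but it leaves T1 and T3 as they are.

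**Conclusion.** The contradiction holds. The named outcome cannot be produced from the patient items given for T1 and T3, and the sick-days item shows that a count is asked for where one is wanted. This is a mismatch between printed statements, not detail left to a fuller document.

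It is a should-fix. It concerns one of seven secondary outcomes, and neither the primary outcomes nor the sample size depends on it. The conclusion itself rests on no assumed figure. Its practical size does, and could be anything from a minor loss of information to a substantial one, because the article gives no event rates, dispersion or correlation.

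**What to change.** **First choice, workable at any stage.**

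- In the Abstract, the Background, the outcome section and the Data analysis plan, replace the number of exacerbations with two separate yes/no outcomes: at least one asthma attack, and at least one acute worsening.
- Compare arms at T3 by logistic or modified Poisson regression, adjusted for the T1 answer to the same item and for clinic.
- Within arms, use McNemar's test instead of the paired t-test.
- Exempt both outcomes from the half-SD rule.
- Draw no conclusion about the number of exacerbations.

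This costs wording only and needs no new data.

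**Alternative, if data collection has not started.** Add a follow-up (*If yes, how many?*) to both items at T1 and T3. Compare arms by negative-binomial regression with the T1 count as covariate and log elapsed time as offset. The cost is two short questions and noisier recalled counts. Table 1 places the implementation phase in 2024. If it is already running, participants enrolled earlier would have no T1 count and would have to be dropped from that model or imputed, so the first choice is then the safer one.
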